# Hyperpure chlorine dioxide versus chlorhexidine in intra-oral halitosis (ODOR trial) – protocol of a double-blinded, double-arm, parallel non-inferiority pilot randomized controlled trial

**DOI:** 10.1038/s41405-024-00221-8

**Published:** 2024-05-20

**Keywords:** Oral diseases, Halitosis

## Abstract

**Introduction:**

Intra-oral halitosis (IOH) is the most common type of bad breath; its consequences impair quality of life. However, evidence-based treatment protocols and guidelines are lacking. Our aim is to investigate the effectiveness of chlorine dioxide as an applicable complementary treatment modality in IOH after tongue cleaning.

**Methods and analysis:**

The ODOR trial will be a single-center, double-blinded, parallel-group, double-armed pilot randomized controlled trial with a non-inferiority design. The efficacy of hyperpure chlorine dioxide will be compared to chlorhexidine mouthwash. We plan to investigate the short-term effects of the intervention over a 3-h period. The primary endpoint will be changes in organoleptic test scores. At the end of the pilot investigation of the first 30 patients each, sample size calculation will be performed. If feasible, the investigators will continue the study by enrolling more patients.

**Trial registration:**

The trial has been registered at ClinicalTrials.gov (NCT06219226).

## Introduction

### Background

The prevalence of halitosis is approximately 31.8% and is constantly increasing [1]. Intra-oral halitosis (IOH) is the most common type of bad breath [2]. The main consequences of halitosis are feelings of inadequacy, depression, anxiety, sensitivity, anger, stress [3], and impaired oral health-related quality of life (OHRQoL) [4].

Mouthwashes are the subsequent treatment of IOH after toothbrushing and tongue cleaning [5–8]; however, guidelines for the management of IOH still do not exist. Several types of mouthwashes are available on the market. Although most of the currently used ones, such as those containing chlorhexidine or alcohol, are effective; however, they are not recommended for daily use due to their potential side effects [9] such as tooth discoloration [10], and false taste sensations [11]. Chlorhexidine is considered to be the gold standard mouthwash for its potent antimicrobial properties and effectiveness in reducing plaque and gingivitis [12]. However, when it comes to intra-oral halitosis, the evidence supporting the efficacy of chlorhexidine is still uncertain [13].

Mouthwashes containing chlorine dioxide (ClO_2_) have a doubled effect of reducing IOH; they reduce the amount of bacteria together with the volatile sulfur compounds [14–16], which are the main components of IOH. Their main advantage is the lack of known side effects and efficacy in low concentrations [17]. Most ClO_2_ mouthwashes contain a stabilized form of ClO_2_ [18–21]. However, they are assumed to be less effective than hyperpure ClO_2_ due to lower concentrations of active ClO_2_ molecules and contamination with other ingredients [14, 22]. In an in vitro study, the hyperpure ClO_2_ solution showed superior effectiveness to chlorhexidine against aerobic bacteria and Candida; furthermore, its biofilm-dissolving effect is significantly higher [23].

Several studies have already investigated stabilized ClO_2_ mouthwashes in IOH [20, 24–27]; a meta-analysis [28] found them effective in halitosis compared to placebo. However, none of the previous studies have investigated the efficacy of a hyperpure version of ClO_2_ in IOH compared to chlorhexidine, which indicates the relevance of this randomized controlled trial (RCT).

### Objectives

We aim to investigate the effectiveness of hyperpure ClO_2_ in IOH with organoleptic measurement as the primary endpoint.

We hypothesize that hyperpure ClO_2_-containing mouthwash is non-inferior to gold standard chlorhexidine mouthwash in IOH, reducing the halitosis level measured by the organoleptic test score.

### Trial design

This study protocol is designed as a pilot, single-center, double-blinded, parallel-group, double-armed RCT with a non-inferiority design. We plan to investigate the short-term effects over a 3-h period.

## Methods

### Study protocol development

The SC and ITAB members developed the first version of the trial protocol following the Standard Protocol Items Recommendations for Interventional Trials (SPIRIT) 2013 Statement [29].

### Study setting

The study will be performed with one urban center at the Department of Restorative Dentistry and Endodontics, Semmelweis University (Budapest, Hungary).

### Eligibility criteria

#### Inclusion criteria

►Aged 18 or older►Organoleptic test score (OLS) ≥ 2 for IOH (A trained dentist will perform the measurements.)►Patients with at least 20 teeth.►Eight hours of use of scented oral hygiene product, 4 h of eating, and 2 h of drinking restriction►Restriction of alcohol, caffeine, perfume usage, and food intake with characteristic smell on the day of investigation

#### Exclusion criteria

►Medical history of systemic and infectious diseases (e.g., hepatitis, HIV, tuberculosis)►Antibiotic use within a month before or during the study or any regular medication►Extraoral halitosis (distinguished by observing the nasal breath)►Eat foods linked to oral malodor (e.g., garlic) on the day before and on the day of sampling, as well as wear heavily fragrant cosmetics on that day►Patients with removable dentures►Smokers (cigars, cigarettes, pipes, chewing tobacco, e-cigarette, or vaping products used in the last month)

### Interventions

The two arms will be the following:Hyperpure ClO_2_ mouthwash (Solumium Coral®)Chlorhexidine mouthwash (Curasept ADS 220®)

Enrollment begins January 18, 2024.

We will perform randomization if eligibility criteria are fulfilled. After baseline data have been recorded, interventions will be performed.The test group will use a 25 ml 10-fold dilution of hyperpure 0.03% ClO_2_ (Solumium Coral®, final concentration: 0.003%) [30], and the control group will use chlorhexidine-containing mouthwashes (Curasept ADS 220, 0.2%). Rinsing will last 2 × 15 s in both groups as recommended by the manufacturer (2 × 12.5 ml) [31]. Intervention and control mouthwashes will be portioned into equally dark glasses.

### Outcomes

#### Primary outcome

The primary endpoint of the study will be the changes in organoleptic test scores as measured by a trained dentist with the gold standard 6-point (0–5) intensity scale [32].

Tests will be performed three times (Table 1): at baseline, immediately after and 3 h after rinsing with mouthwash. Two changes will be measured between the following time points: 1) baseline - immediately after rinsing, and 2) baseline - 3 h later; as suggested by Yaegaki et al. in their halitosis research [33].

**Table 1 Tab1:** Participant timeline.

			Study period			
	Enrollment	Allocation	Post allocation			Close-out
Time point	Starting from January 18, 2024	Baseline	Intervention	Immediately after mouthwash use	3 h later	December 1, 2025
Enrollment:						
Eligibility screen	X					
Informed consent		X				
Randomization		X				
Interventions:						
Hyperpure chlorine dioxide			X			
Chlorhexidine			X			
Assessments:						
Organoleptic score	X	X		X	X	
Volatile sulfur compound measurement with a gas chromatograph		X		X	X	
Self-perceived halitosis		X		X	X	
Subjective experiences, adverse events				X	X	
Statistical analysis						X

Schedule of enrollment, interventions, and assessments.

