##### Statistical methods

We will report on baseline characteristics and differences between the two arms. For continuous primary and secondary endpoints, we will report the mean results of the groups and changes at the different time points. Due to the non-inferiority study design, we choose the non-inferiority limit (*d* = 1) as the most considerable clinically acceptable difference. For the side-effect questionnaire, we will create a summary table showing the frequency of adverse events and all patient comments. In the case of any missing data, sensitivity analyses will be conducted to determine the most suitable approach.

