##### Public and patient involvement

The protocol development phase involved three patients. We asked them to read the patient information leaflet and give informed consent after being introduced to the purpose, primary outcome, and protocol of the study. They thought that the written materials were transparent and informative. Our clinical question was deemed highly relevant by the patients. They said that the one-day caffeine restriction was too long, and that they could not imagine not brushing their teeth the night before the investigation. Thus, we reduced the time limits in the protocol, oral hygiene restriction from 12 to 8 h, and caffeine from one day to the day of the investigation. In addition, they expressed their preference for flavored mouthwashes.

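### The primary endpoint is two unranked changes in organoleptic score with one margin, and nothing says which change, or whether both, decides non-inferiority or drives the sample-size step

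*Protocol article*

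**What the plan says.** Primary outcome: "The primary endpoint of the study will be the changes in organoleptic test scores", scored by a trained dentist from 0 to 5. The section then lists the comparisons: "Two changes will be measured between the following time points", the first from baseline to just after the rinse and the second from baseline to 3 h. It cites earlier halitosis research for this choice and gives no order of importance.

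Statistical methods: "we choose the non-inferiority limit (*d* = 1) as the most considerable clinically acceptable difference". There is one margin, attached to neither change.

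Objectives: the hypothesis is that chlorine dioxide is non-inferior to chlorhexidine in "reducing the halitosis level measured by the organoleptic test score", again without a time point.

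Trial design: "We plan to investigate the short-term effects over a 3-h period". This gives the length of follow-up. It does not make 3 h the deciding time.

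Sample size: after 30 participants per arm, the primary-outcome results are to be used to estimate the sample size. If the trial goes on, the pilot becomes an interim analysis.

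Inclusion criteria: before assessment there is a restriction worded as "Eight hours of use of scented oral hygiene product", and perfume is restricted on the day. The Exclusion criteria add heavily fragrant cosmetics.

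**The concern.** The choice of primary time point and the rule for success are part of the endpoint definition. The Primary outcome section sets that definition and leaves it open. Three readings fit the text equally well: 3 h decides, either change decides, or both must meet the margin. They differ in error rate, in power and in what a positive result would mean.

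The gap carries into the Sample size section. Two changes with different SDs and different effects give two sample sizes and two interim readings. With no rule fixed beforehand, the deciding change could be picked after data from 60 participants (2 × 30) have been seen.

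A second, weaker consideration concerns the immediate score. The protocol keeps outside scents away from the organoleptic assessment, then has breath scored directly after one of two different mouthwashes. The article describes no odor matching, washout or water rinse. The immediate score may therefore be affected by residual product odor or by masking.

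**Working it through.** **Inputs from the article.** Two changes (Primary outcome); margin d = 1 (Statistical methods); n = 30 per arm (Sample size). There is no alpha, SD, power or calculated sample size, so there is no figure to reproduce.

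**Assumptions.** One-sided alpha 2.5% per comparison (5% shown as an alternative); SD of change 1 to 2 points, equal in both arms; correlation ρ between the two estimated differences from 0 to 0.9; normal approximation.

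**1. Error of an either-or rule when both true differences equal the margin.** Error = 1 − P(Z1 < 1.96, Z2 < 1.96) for a bivariate normal with correlation ρ. At ρ = 0 this is 1 − 0.975² = 0.0494.

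| ρ | one-sided 2.5% | one-sided 5% |
|---|---|---|
| 0 | 4.94% | 9.75% |
| 0.3 | 4.76% | 9.29% |
| 0.5 | 4.54% | 8.78% |
| 0.7 | 4.17% | 8.04% |
| 0.9 | 3.52% | 6.81% |

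**2. No difference immediately, full margin at 3 h.** Take a true immediate difference of 0 and a true 3-h difference of 1 against chlorine dioxide. The immediate comparison meets the margin with probability Φ(d/SE − 1.96), where SE = SD × √(2/30) = 0.2582 × SD.

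| SD | SE | 1/SE − 1.96 | probability |
|---|---|---|---|
| 1.0 | 0.258 | 1.91 | 97.2% |
| 1.2 | 0.310 | 1.27 | 89.8% |
| 1.5 | 0.387 | 0.62 | 73.3% |
| 2.0 | 0.516 | −0.02 | 49.1% |

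Counting success at either time barely changes this: for ρ of 0.3 to 0.7 it is 97.2% (SD 1), 73.3–73.5% (SD 1.5) and 49.1–49.7% (SD 2). If 3 h alone decides, the probability is 2.5%.

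**3. Cost of requiring both.** With both true differences 0, power at a single named time point equals the last column above. If both must meet the margin, with ρ from 0.3 to 0.7, power is 94.7–95.4% (SD 1), 81.8–84.3% (SD 1.2), 57.2–63.0% (SD 1.5) and 28.9–36.4% (SD 2). The error stays at or below 2.5%.

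**4. Why the sample-size step needs a named change.** For a true difference of 0 and 80% power, n per arm = 2 × (1.96 + 0.84)² × SD² / d², rounded up. This gives 16 for SD 1, 36 for SD 1.5 and 63 for SD 2. If the two changes have different SDs, the answer depends heavily on which one is used.

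**The case against.** **This is an exploratory pilot, and a fuller document may hold the rule.** Both are fair points. But the article states a non-inferiority hypothesis and a margin, and lets the pilot become the interim analysis of a larger trial. An unseen analysis plan might add a rule; the endpoint definition shown here leaves the time point open.

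**No either-or rule is stated.** This stands. A reader might infer that the sponsor intends to claim success on whichever change succeeds. The article does not say so; it only leaves room for it. The error figures show what the wording permits.

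**The calculations rest on assumptions.** This also stands. Alpha, SD and correlation are all absent from the article. The two changes share a baseline, so a high correlation is plausible, and at 0.9 the error is 3.5%. The 97% falls to 49% as the SD goes from 1 to 2.

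**The smell argument.** A reader might infer that the immediate score simply reflects mouthwash smell, and that masking makes the arms look alike and so favors non-inferiority. The documents do not support this. They describe the odor of neither product and give no reason for the scent restrictions, which concern outside exposures. The shortening of the oral hygiene limit from 12 to 8 h followed patient feedback and says nothing about scent interference. The Background also offers a route to a real immediate effect, since chlorine dioxide is said to reduce volatile sulfur compounds. Two different products may mask unequally: more masking by chlorhexidine would bias against chlorine dioxide, and more by chlorine dioxide would bias in its favor. What remains is a possibility of unknown direction.

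**The cited research supports both time points.** It may justify measuring both. It does not settle which of them decides.

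**Conclusion.** The point holds as a defect in the endpoint definition: two unranked primary changes, one margin, and no rule for the non-inferiority decision or the sample-size and interim step. At an assumed one-sided 2.5% per comparison, an either-or reading raises the error to about 3.5–4.9% when both true differences sit at the margin.

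The larger issue is what the claim would mean. With no true difference immediately and a full-point deficit at 3 h, the immediate comparison would meet the margin with probability 97%, 90%, 73% or 49% at assumed SDs of 1, 1.2, 1.5 or 2, against 2.5% if 3 h decides. That scenario is illustrative; nothing in the documents shows that it is likely.

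Possible odor or masking at the immediate score is a secondary inference from the protocol's own scent restrictions. It is a reason for caution about letting that score carry the claim alone. It does not establish that the immediate time point is invalid, or that it favors either arm.

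**What to change.** Before any unblinded pilot analysis, amend the protocol and the registration to:

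- name the baseline-to-3-h change in organoleptic score as the single primary endpoint, tie d = 1 to it, and state the one-sided level;
- use that same change for the sample-size estimate and any interim reading;
- make the immediate change secondary, tested at the same level only if the 3-h comparison succeeds, and read it alongside the GC/MS sulfur compounds already collected at that time.

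The choice of 3 h fits the stated aim of studying effects over 3 hours. Requiring both changes to meet the margin would also control the error and keep the two-time-point endpoint, but it costs power (for example 57–63% instead of 73% at SD 1.5) and leaves the possibly odor-affected score co-decisive.

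The cost is wording; every measurement stays. The small downside is that an immediate effect alone can no longer carry the primary claim.

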#### Secondary outcomes

We plan to measure the changes in volatile sulfur compounds, such as hydrogen sulfide, methyl mercaptan, and dimethyl sulfide with gas chromatography-mass spectrometry (GC/MS) at the same time points as the primary endpoint. It is an instrumental technique comprising a gas chromatograph coupled to a mass spectrometer, which allows complex mixtures of chemicals to be separated, identified and quantified. Calibration will be performed with a gas mixture produced by Linde (100 ppb H_2_S, 500 ppb CH_3_SH, 1000 ppb (CH_3_)_2_S). Samples will be collected in Teflon-coated bags and delivered to the measurement site immediately after sampling.Self-perceived halitosis. We will collect these data on a visual analog scale (Slider (RedCAP), visual analog scale coded as values 0–100) at the time mentioned above.Side effects. (e.g., tooth discoloration, signs of allergic reactions, subjective experiences: unpleasant taste, false taste or burning sensation, pain, and changes in salivary flow).

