##### Safety and adverse events

Side effects of chlorine dioxide at this low concentration are not known yet [28]. Prolonged use of CHX-containing mouthwash can lead to several adverse events with a relatively high frequency and it is hypothesized that a specific type of control mouthwash may have fewer undesirable effects [12]. We will ask the patients about their experiences at each time point. If patients experience any adverse events, we will record these follow-up questionnaires. SC will verify the validity of adverse events; the relevant ones will be reported to the National Institute of Pharmacy and Nutrition (OGYÉI). If any safety concerns arise, we will stop the study immediately.

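### Table 1 and the safety section disagree on whether symptoms are asked before the rinse; without a baseline, the side-effect table may mix existing complaints with new ones

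*Protocol article*

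**What the plan says.** The Secondary outcomes section of the protocol article names side effects as an outcome. Among its examples, under subjective experiences, are "false taste or burning sensation, pain, and changes in salivary flow".

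Two places govern when these are collected:

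- **Safety and adverse events section:** "We will ask the patients about their experiences at each time point".
- **Table 1 (Primary outcome section):** the row "Subjective experiences, adverse events" is marked immediately after mouthwash use and at 3 h. Its baseline cell is empty.

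The time points are set out in the Primary outcome section: "Tests will be performed three times (Table 1): at baseline, immediately after and 3 h after rinsing with mouthwash". The other three assessments in Table 1 (organoleptic score, volatile sulfur compounds, self-perceived halitosis) all carry a baseline mark.

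For the analysis, the Statistical methods section states that "we will create a summary table showing the frequency of adverse events and all patient comments". On review of events, the safety section adds that "SC will verify the validity of adverse events".

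**The concern.** Table 1 and the safety section can lead staff to collect different data. Someone who works from Table 1 asks about symptoms twice, both times after exposure. Someone who works from the safety text, with the three time points in mind, asks three times.

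If Table 1 prevails, the state before the rinse is not recorded in this row, and a form that was never filled in cannot be recovered at analysis. That matters here because complaints before the rinse are plausible. Participants are selected for oral malodour, and the eligibility criteria have them arrive after 8 h without scented oral hygiene products, 4 h without food and 2 h without drink. Unpleasant taste or a dry mouth could well be present before any mouthwash is used, and taste and salivary complaints are on the side-effect list.

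At stake is the reading of the side-effect table. The safety section says that side effects of chlorine dioxide at this concentration are not yet known, and this table is the planned summary of them. A frequency per arm that contains background complaints would overstate how often each product causes symptoms and would blur the difference between the products.

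**Working it through.** The plan states no figure for side effects, so there is none to reproduce. The check is a comparison of sections, followed by an illustration of scale.

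**Step 1. Compare the schedule.**

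| Item | Baseline | Immediately after | 3 h |
|---|---|---|---|
| Time points, Primary outcome section | yes | yes | yes |
| Organoleptic score, volatile sulfur compounds, self-perceived halitosis (Table 1) | yes | yes | yes |
| Subjective experiences and adverse events (Table 1) | no | yes | yes |
| Safety section, read literally | yes | yes | yes |

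Rows 3 and 4 differ in the baseline column. They agree only if the safety section means the time points already marked in its own Table 1 row. In that case there is no contradiction, but there is no baseline either.

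**Step 2. Look for another source of the pre-rinse state.** The Interventions section says that baseline data are recorded before the rinse, but not that symptoms are among them. The data collection forms are in a supplement that is not shown. The Statistical methods section plans a frequency table and states no rule that an event must be new or worse.

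**Step 3. Effect on the table if prior complaints are recorded without asking about onset.** Inputs:

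- n = 30 per arm, from the Sample size section.
- b = proportion with the complaint before the rinse, taken as equal in both arms because of randomisation. The documents give no value; 10% to 30% is an assumption for illustration.
- p = risk that the rinse causes the complaint. It is left as a symbol, because the documents give no value.

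Observed frequency in an arm: p_obs = b + (1 − b)p.

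Excess over the true risk: p_obs − p = b(1 − p). This is never negative, so each arm's frequency is inflated.

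Difference between arms: (1 − b)(p_test − p_control). The b term cancels, so neither product is favoured in expectation, but the difference is multiplied by (1 − b).

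| Assumed b | Participants per arm counted whatever the product does (30 × b) | Factor on the between-arm difference (1 − b) |
|---|---|---|
| 10% | 3 | 0.90 |
| 20% | 6 | 0.80 |
| 30% | 9 | 0.70 |

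**Step 4. What a baseline would restore.** Counting only new complaints gives (1 − b)p over all participants, which removes the inflation but not the dilution. Counting new or worse complaints gives (1 − b)p + bp = p, if worsening among those already affected occurs and is captured at the same rate p. The form therefore needs to show worsening as well as presence.

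**The case against.** The strongest reply is that post-exposure collection of side effects is ordinary, and that the plan already contains safeguards. The steering committee reviews the validity of events, the forms may ask about onset, and the randomised control arm carries the same background. One can also say that nobody has experiences of a mouthwash before using it, so the safety sentence may never have meant baseline. Finally, the exclusion of systemic disease, regular medication, smoking and removable dentures makes prior oral symptoms less common.

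Much of this stands. It limits the size of the problem and rules out an expected bias toward either arm. It does not settle which schedule applies. Under Table 1 the committee would have no scheduled record of the pre-rinse state against which to judge a report. Randomisation protects the direction of the contrast, but not the per-arm frequencies that the table will show.

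Three stronger readings are tempting, and the documents do not support them:

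- **That prior symptoms are counted as product effects.** No section states such a rule. They may be counted, depending on forms that are not shown and on the committee's review.
- **That change in salivary flow cannot be obtained.** It is listed as a subjective experience. A patient can be asked after the rinse whether there is more or less saliva than before, and the article plans no measured flow rate to subtract.
- **That the tooth-discoloration item or zero counts in 30 participants will support a false claim of no difference.** The side-effect list is given as examples, the article plans no such claim, and small-sample bounds have nothing to do with the missing baseline.

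**Conclusion.** The point holds as a minor inconsistency with a practical consequence. Table 1 schedules no symptom enquiry before the rinse, while the safety text, read with the three named time points, includes one. If Table 1 is followed, the side-effect frequencies may include taste, burning, pain or salivary complaints that were already there. The result would be inflated frequencies within each arm and a diluted difference between arms, with no expected advantage to either product.

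The size is unknown. The 3 to 9 participants per arm and the factor of 0.90 to 0.70 rest on an assumed 10% to 30% prevalence, on equal prevalence in the two arms, and on prior complaints being recorded without a question about onset. If the unseen forms ask about onset, or if baseline is in fact asked, the effect is smaller or absent and only the wording needs correction. The primary outcome is not affected.

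**What to change.** Reconcile Table 1 with the safety section:

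1. Mark the row for subjective experiences and adverse events at Baseline in Table 1, with the same REDCap form completed before the rinse.
2. State in the Statistical methods section that an item is tabulated as a side effect only if it is new or worse than at baseline, and make sure the form can show worsening.

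The cost is one more short form per participant, one cell in Table 1 and one sentence of analysis text. For participants already seen without a baseline form, the pre-rinse state cannot be restored, and the table should say for whom it is missing.
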